### Sample size determination with statistical power calculation

Data will be obtained from 712 families at baseline, with 2 children and up to 2 parents per family (given divorce rates, 1.66 parents per family are estimated). Stratification will be used to over-select female service members and high-risk families such that 456 families will have female military parents and 356 families will be high risk. Power is calculated for three types of analytic samples:

A baseline/cross-sectional analysis sample of 712 families and 1,424 children (2 per family), and 1,182 parents (1.66 per family);A panel analysis sample composed of families who participate at both waves of the study. Based on experience and other military studies [44], 75% retention is projected, resulting in 534 families, 1,068 children, and 887 parents at Wave 2;A repeated measures sample, comprising all observations from both waves. With a 75% family retention rate, the sample will include 1,246 (= 712 + 534) repeated family observations and 2,670 repeated child observations, and 2,216 repeated parent observations. The repeated measures sample will be the priority sample for testing study hypotheses.

Effective sample sizes are calculated for a two-level, mixed-effects model per Snijders [45] using an estimated within-family ICC = 0.30. Power is estimated for a standardized regression coefficient in a model with 5 covariates and alpha = 0.05. Effect sizes detectable at .80 power are listed in Table 1.

**Table 1 pone.0295007.t001:** Detectable effect sizes.

Direct, Moderation, and Mediation Effects (n = cross-sectional / panel / repeated)	Detectible Standardized Beta		
	Cross- sectional	Panel	Repeated Measures
**1. Family level predictors** (n = 712 / 534 / 1246; effective n = 1095 / 822 / 1917)	0.085	0.098	0.064
**2. Child level predictors** (n = 1424 / 1068 / 2492; effective n = 2034 / 1526 / 3560)	0.063	0.072	0.047

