**Simple Effects**			
**3. Family level predictors within risk and sex groups** (n = 356 / 267 / 623; effective n = 548 / 411 / 958)	0.120	0.139	0.091
**4. Child level predictors within risk and groups** (n = 712 / 534 / 1246; effective n = 1017 / 763 / 1780)	0.088	0.102	0.067

Power for tests 1 and 2 in the table apply to direct effects (**Aim 1** paths in Fig 1); mediation effects (products of path coefficients; **Aim 2** paths in Fig 1), and moderating effects (differences in slopes/interactions; **Aim 3** paths in Fig 1); Tests 3 and 4 represent simple slopes for associations within levels of the moderators family risk status and service member sex, which represent the lowest powered tests.

Some cite 0.10 as a “small” effect size for a partial correlation, which is comparable to a standardized beta coefficient [46]. Recent findings about effects of recent deployment (duration, trauma) effects on military youth outcomes gave standardized beta effect estimates in the range of 0.18 to 0.32, on average [44]. These reported effects were controlling for baseline levels in child outcomes and therefore represent effects on residual change, giving confidence that the study is adequately powered. Importantly, power will be further increased through the use of latent variables, which increase measure reliability [47], correlated mediators and outcomes in multivariate analyses [48], and including control variables that explain variance in mediators/outcomes (particularly true in panel analyses). However, power may decrease due to the unequal weighting effect [49].

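### Table 1's detectable betas hold for a standardized product term, but the text also applies them to differences in slopes, where two-group moderators need about twice the tabulated value

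*Protocol article*

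**What the plan says.** The section on sample size and power in the protocol article fixes the metric: "Power is estimated for a standardized regression coefficient in a model with 5 covariates and alpha = 0.05". It adds that "Effect sizes detectable at .80 power are listed in Table 1". Effective sample sizes are computed "using an estimated within-family ICC = 0.30".

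Row 1 of Table 1 (family-level predictors) lists "n = 712 / 534 / 1246; effective n = 1095 / 822 / 1917" with detectable betas 0.085 / 0.098 / 0.064. Row 2 (child-level predictors) has effective n 2034 / 1526 / 3560 and betas 0.063 / 0.072 / 0.047. Row 3 (family-level predictors within risk and sex groups) has "effective n = 548 / 411 / 958" and betas 0.120 / 0.139 / 0.091. Row 4 (child level, within groups) has 1017 / 763 / 1780 and 0.088 / 0.102 / 0.067.

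The text below the table extends rows 1 and 2 to direct effects, mediation effects "and moderating effects (differences in slopes/interactions", the last being Aim 3. It describes rows 3 and 4 as "simple slopes for associations within levels of the moderators family risk status and service member sex, which represent the lowest powered tests".

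The analysis section for Aim 3 tests parent and child sex by multi-group models, with likelihood ratio tests of equal against unequal effects. Continuous moderators (vulnerability, support) are tested through conditional effects.

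**The concern.** A difference between two independently estimated slopes carries the sampling error of both. It cannot be detectable at the value that applies to a single slope estimated from everyone, and it cannot be easier to detect than the slope within one of the two groups. The text under Table 1 implies both.

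The comparison of mothers' and fathers' deployments is a stated purpose of the design. Female service members were oversampled for it, and the Innovation section presents it as a strength. A reader who takes row 1 at its word would believe that a slope difference of 0.064 between mothers and fathers is detectable with 80% power in the priority repeated-measures sample. The same reader would take the simple slopes as the worst case when judging a null moderation result.

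**Working it through.** **Inputs, all from the sample size section and Table 1.** Power 0.80; alpha 0.05 (taken as two-sided, see step 1); ICC 0.30; the effective n of rows 1 to 4; 456 of 712 families with a female military parent, leaving 712 − 456 = 256; 356 of 712 families high risk, so risk is split 50:50.

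**1. Reproduce the table.** The effective n follow from 2 × families / 1.3 (2 × 712 / 1.3 = 1095) and children / 0.7 (1424 / 0.7 = 2034). With k = 1.960 + 0.842 = 2.802, detectable beta = k / √(effective n):

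| Row | Computed | Stated |
|---|---|---|
| 1 | 0.0847 / 0.0977 / 0.0640 | 0.085 / 0.098 / 0.064 |
| 2 | 0.0621 / 0.0717 / 0.0470 | 0.063 / 0.072 / 0.047 |
| 3 | 0.1197 / 0.1382 / 0.0905 | 0.120 / 0.139 / 0.091 |
| 4 | 0.0879 / 0.1014 / 0.0664 | 0.088 / 0.102 / 0.067 |

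All 12 cells agree within 0.001. One-sided alpha would give 0.075 in the first cell and does not fit. Each cell is therefore the detectable size of one coefficient.

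**2. Difference between two equal groups.** SE = √(1/n₁ + 1/n₂), with the half-sample effective n of rows 3 and 4; detectable difference = k × SE.

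- Family level: k√(2/548) = 0.169; k√(2/411) = 0.195; k√(2/958) = 0.128.
- Child level: k√(2/1017) = 0.124; k√(2/763) = 0.143; k√(2/1780) = 0.094.

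These are 2.0 times the computed values for rows 1 and 2. The same follows from the printed row 3: √2 × 0.120 = 0.170 and √2 × 0.091 = 0.129.

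**3. Parent sex at 456/256.** With shares q = 0.640 and 0.360, the multiplier on the single-coefficient value is 1/√(q(1−q)) = 2.084, assuming equal retention in both groups.

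- Family level: 0.176 / 0.204 / 0.133.
- Child level: 2.084 × 0.0621 = 0.129; 2.084 × 0.0717 = 0.149; 2.084 × 0.0470 = 0.098.

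**4. Power if the true difference equals the tabulated value.** Family level, cross-sectional: SE = √(2/548) = 0.0604; Φ(0.085/0.0604 − 1.96) = Φ(−0.55) = 0.29. The other five cells of rows 1 and 2 give 0.29 to 0.30. At the parent-sex split the range is 0.27 to 0.28. A least-squares simulation at n = 1095 gave 29.4% for a difference of 0.085. An effective n of 4 × (2.802/0.085)² ≈ 4,345 would be needed for 80%.

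**5. Where rows 1 and 2 are right.** In the same simulation, a product-term coefficient of 0.085 had 80.0% power with a continuous standardized moderator and 80.4% with a binary moderator coded ±1. In the ±1 coding the coefficient is half the slope difference, so 0.085 there means a difference of 0.17.

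**6. Which test is weakest.** Cross-sectionally at family level, the simple slope needs 0.120 and the difference needs 0.169. At a difference of 0.120, power is Φ(0.120/0.0604 − 1.96) = 0.51.

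**7. At the article's own benchmark of 0.10 for a small effect.** Power for a slope difference of 0.10 at a 50:50 split is 38% / 30% / 59% at family level and 62% / 50% / 85% at child level.

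**The case against.** The strongest reply is that the table never left its own metric. The section states that power is for a standardized regression coefficient, and the column heading says the same. For an interaction, that coefficient belongs to the standardized product term, and for that the values are correct. On this reading the mention of slope differences only explains what moderation means, and rows 3 and 4 do show the largest detectable betas. This stands for the continuous moderators, vulnerability and support, which are a large part of Aim 3. Taking moderation out of rows 1 and 2 altogether would therefore withdraw a correct statement.

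It does not rescue the rest. The text names slope differences and gives family risk status and service member sex as the moderators. Rows 3 and 4 are in within-group slope units, so a reader will compare them directly with a difference between those slopes. The multi-group tests of sex are comparisons of that kind.

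A reader might also infer that Aim 3 has about 29% power. The article does not support that: it assumes no effect size for Aim 3, and 29% applies only if the true difference equals the tabulated value. For a slope difference of 0.18 in the repeated-measures sample, power at a 50:50 split is about 98% at family level and above 99% at child level. That 0.18 is the lower end of cited deployment effects, not interactions, so it does not show adequacy either.

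Nor does the article propose to infer moderation from one significant and one non-significant simple slope. The likelihood ratio tests for Aim 3 are already difference tests, and the analysis section puts the focus on effect sizes and confidence intervals.

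**Conclusion.** The point holds for two-group moderators. Every cell of Table 1 is correct for a single standardized coefficient. The error is in the scope that the text gives to rows 1 and 2. Read as differences in slopes, the detectable values are understated by a factor of 2.0 for an equal split and 2.08 for the stated parent-sex split. Power at the tabulated values is then about 29% and 27% instead of 80%. The statement that the simple slopes are the lowest powered tests is wrong for the same reason.

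The figures assume two-sided alpha of 0.05, the article's effective n at face value (including its treatment of repeated observations), equal residual variance in the groups, and a predictor with the same spread in each group. They do not cover child sex. It can differ between siblings, so its design effect may not be the one used here, and the article gives no figure from which to compute it. Sample size, tests and decision rules are unaffected.

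**What to change.** - Below Table 1, state that for moderation rows 1 and 2 refer to the coefficient of a standardized product term, which is half the slope difference for an equally split binary moderator.
- Add rows to Table 1 for the two-group slope difference (cross-sectional / panel / repeated measures). For a 50:50 split such as risk group: 0.169 / 0.195 / 0.128 at family level and 0.124 / 0.143 / 0.094 at child level. For parent sex at 456/256: 0.176 / 0.204 / 0.133 and 0.129 / 0.149 / 0.098.
- Delete the clause that calls the simple slopes the lowest powered tests.

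The cost is a sentence and a few table rows. The stated sensitivity for binary moderators becomes less favourable. No new data are needed and the Aim 3 tests stay as they are.

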#### Analyses for aim 2: To assess the role of parents’ psychological health and family processes in mediating relationships between siblings’ early exposures to parental deployment and later youth adjustment

This aim highlights four indirect pathways through which deployment(s) influence youth adjustment. Deployment factors studied in Aim 1 are expected to be negatively related to parents’ psychological health, parental efficacy, marital relationship quality, and family functioning at Time 1, which in turn will be positively related with youth adjustment at Time 2. The magnitude and statistical significance of the indirect effects of deployment through each of these processes will be tested using the INDIRECT command within Mplus, which employs a product of coefficients method of testing mediation [121] and the bootstrap method to compute standard errors for the significance test [122]. Importantly, the four indirect pathways will be tested concurrently, highlighting not only which pathways are critical for understanding the potential enduring effects of parental deployments on youth adjustment, but also the relationships among them. Differences across siblings also will be assessed.

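### Correlation among the four mediators is listed as a power gain, but for the per-pathway tests of Aim 2 it lowers power, and Table 1 makes no allowance for it

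*Protocol article*

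**What the plan says.** The power model is a single coefficient: "Power is estimated for a standardized regression coefficient in a model with 5 covariates and alpha = 0.05". Effective sample sizes are derived "using an estimated within-family ICC = 0.30", and "Effect sizes detectable at .80 power are listed in Table 1".

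The text below Table 1 says that the first two rows also cover "mediation effects (products of path coefficients"). It then lists features expected to raise power beyond the table: "power will be further increased through the use of latent variables, which increase measure reliability [47], correlated mediators and outcomes in multivariate analyses [48"]. The only feature named as a possible loss is unequal weighting.

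The analysis section for Aim 2 places parents' psychological health, parenting efficacy, couple relationship quality and family functioning at Time 1, and youth adjustment at Time 2. It tests the size and significance of the indirect effect through each process and adds: "Importantly, the four indirect pathways will be tested concurrently, highlighting not only which pathways are critical".

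**The concern.** A specific indirect effect is the product of a deployment-to-mediator path (a) and a mediator-to-outcome path (b). With four mediators in one outcome equation, each b is a unique effect with the other three held constant. Correlated predictors share information, so each unique effect is estimated less precisely. On the a side, every mediator is regressed on the same deployment predictors, so joint estimation gives essentially no gain for individual coefficients. One component loses and the other does not gain, yet the article counts the correlation as a benefit.

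At stake is how a null result for a pathway is read. Two overlapping pathways may both be active while neither reaches 0.05 alone. A reader who has been told that correlation among mediators helps power is more likely to take such a result as evidence that the pathway does not operate.

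**Working it through.** **Inputs from the article.** Alpha 0.05; power 0.80; within-family ICC 0.30; 534 panel families with 2 children each; panel detectable betas 0.098 (family level) and 0.072 (child level). The panel column applies because mediators are taken at Time 1 and outcomes at Time 2.

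**Input assumed.** Equal pairwise correlation r among the four mediators. The article gives no value.

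**Step 1: reproduce Table 1.**
- Family-level effective n = 2N/(1 + ICC) = 2 × 534/1.3 = 821.5. Table 1 lists "effective n = 1095 / 822 / 1917".
- Child-level effective n = 2N/(1 − ICC) = 2 × 534/0.7 = 1525.7. Table 1 lists "effective n = 2034 / 1526 / 3560".
- Detectable beta, two-sided = (1.960 + 0.842)/√n. This gives 0.0977 at n = 822 and 0.0717 at n = 1526, against 0.098 and 0.072.

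All 12 entries reproduce to within 0.001. The formula has no term for correlation among predictors, so the table neither credits nor charges for it.

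**Step 2: four concurrent mediators.** The R² of one mediator on the other three is 3r²/(1 + 2r), and VIF = 1/(1 − R²). The detectable unique beta is multiplied by √VIF. Power at the original beta is Φ(2.802/√VIF − 1.960).

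| r | R² | VIF | Detectable beta, family level | Detectable beta, child level | Power at the original beta |
|---|---|---|---|---|---|
| 0 | 0 | 1.00 | 0.098 | 0.072 | 80% |
| 0.3 | 0.169 | 1.20 | 0.107 | 0.079 | 72% |
| 0.4 | 0.267 | 1.36 | 0.114 | 0.084 | 67% |
| 0.5 | 0.375 | 1.60 | 0.124 | 0.091 | 60% |
| 0.6 | 0.491 | 1.96 | 0.137 | 0.101 | 52% |

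For example, at r = 0.5: 3 × 0.25/2 = 0.375; 1/0.625 = 1.60; 0.0977 × 1.265 = 0.124; Φ(2.802/1.265 − 1.960) = Φ(0.255) = 60%.

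**Step 3: simulation.** The table above ignores outcome variance explained by the other three mediators. A simulation that includes it used n = 822, 3,000 replicates and single-level data, with r as the mediators' correlation given deployment. A pathway counted as detected if both a and b were significant.

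| a, b | Power for | r = 0 | r = 0.3 | r = 0.5 | r = 0.7 |
|---|---|---|---|---|---|
| 0.098, 0.098 | a path | 81% | 80% | 80% | 81% |
| 0.098, 0.098 | b path | 81% | 75% | 64% | 46% |
| 0.098, 0.098 | specific indirect effect | 66% | 60% | 51% | 37% |
| 0.098, 0.098 | total indirect effect | 99.7% | 97% | 92% | 87% |
| 0.18, 0.098 | specific indirect effect | 80% | 74% | 63% | 45% |
| 0.18, 0.18 | specific indirect effect | 99.9% | 99.9% | 99.9% | 98% |

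The a path does not move with r; the whole loss is in b. The 66% at r = 0 arises because both paths must be significant, not because of correlation.

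**The case against.** The strongest reply is that the sentence pairs mediators with outcomes and speaks of multivariate analyses, so it may treat mediators as dependent variables or have joint tests in mind. Part of this stands. With effects of one sign, a joint test of the four b paths gains from positive correlation, and a multivariate test of the a paths gains under some effect patterns. It does not rescue the sentence. The text is not limited to joint tests, individual a coefficients gain essentially nothing when predictors are shared, and Aim 2 tests each pathway. Full-information maximum likelihood can recover some item-missing information from correlated mediators, but that gain is incidental.

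A second reply concerns scale. Several parenting and family measures are youth-reported, so the child-level row may apply. There the detectable beta at r = 0.5 is 0.091, still below the 0.10 that the article mentions as small. This stands. The article also treats a standardized beta as comparable to a partial correlation, and in that metric the detectable value depends on n alone. But Table 1 is stated in betas, and a given unique beta corresponds to a smaller partial correlation as r rises.

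Third, the article cites betas of 0.18 to 0.32, and at 0.18 on both paths the loss is negligible. Those figures are effects of deployment on youth outcomes, however, not mediator-to-outcome paths with three other mediators held constant, so they cannot simply be carried over to b.

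Two stronger readings are tempting and are not supported. A reader might infer that the sample size depends on this claim. It does not: the 712 families and all of Table 1 take no credit for it. A reader might also infer that the plan will declare non-significant pathways inactive. It has no such rule. It puts the focus on effect sizes and confidence intervals, and Aim 2 also looks at relationships among the pathways.

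**Conclusion.** The point holds as a misstatement of direction for the tests that Aim 2 specifies. For a given unique effect, correlation among concurrently entered mediators lowers the power of each mediator-to-outcome path and so of each specific indirect effect, and Table 1 does not allow for this.

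At the panel family-level beta of 0.098, power falls from about 80% to 72–75% at r = 0.3 and 60–64% at r = 0.5; the lower figures come from the formula and the upper from the simulation. These sizes rest on an assumed equal correlation. The loss is modest at r of 0.3 or below, material at 0.5 or above, and of little consequence if both paths are near 0.18. It does not show that the study is underpowered for mediation, and it does not touch what the same sentence says about latent variables, correlated outcomes or control variables.

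**What to change.** In the text below Table 1, remove correlated mediators from the list of power gains, or limit the statement to joint tests. Name collinearity among mediators as a loss beside the unequal weighting caveat. Give detectable betas for a single pathway over a range of r, for instance 0.3 to 0.6 as tabulated above, for both family-level and child-level predictors.

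In the Aim 2 analysis, also report the total indirect effect through the four mediators jointly. Overlapping pathways that each miss 0.05 are then not read as absence of mediation. In the simulation with both paths at 0.098, the total effect kept 92% power at r = 0.5, against 51% for a specific effect. Single-mediator models may be shown only as descriptive, because they credit one pathway with the effect of others correlated with it.

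The cost is a slightly less favourable stated figure and one more result to report. No new data are needed, and the sample size and Table 1 stay as they are.

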### Recruitment and consent procedures

After the sampling frame was received in the fall of 2020, public records searches were undertaken to verify and update addresses, and recruitment began, using evidence-informed procedures similar to those previously approved by regulatory authorities for use in studies of military populations (e.g., our preliminary studies, Millennium Cohort Study) [50].

Beginning in the spring of 2023, eligible participants received a series of communications: **A)** A printed postcard indicating that an invitation to participate will be coming; **B)** A hard-copy packet of recruitment materials including an invitation letter and a Frequently Asked Questions brochure inviting the military parent, his or her spouse, and two children to participate. If multiple children are eligible, the youngest two are invited to participate (to minimize the likelihood of ‘aging out’ or leaving home before the end of the study). Separate packets are included for spouses and children, along with a small preincentive [51]. Families are asked to indicate interest by calling an telephone number, sending email to a specified address, returning a reply card, or visiting a website; **C)** A series of email or postcard reminders that include links to the study website; and **D)** A limited sequence of telephone call attempts to invite participation and respond to questions.

#### Parent screening

When a family indicates interest, a screening call is scheduled with the military parent to verify stratification variables and living situation of youth. Screening for adversity consists of asking military parents if they experienced any of 8 specified adverse experiences prior to joining the military. Because participants have not yet given informed consent, they are not asked which specific events occurred or when (detailed questions are asked during the survey and interview). If all criteria are met, and the study has capacity in the appropriate risk stratification group, researchers confirm the family’s eligibility for the study. To give the military parent time to discuss participation in the study with the rest of the family, a follow-up call is scheduled one to two weeks after the screening call. If the family is willing to participate, we ask the military parent to provide informed consent for their own and their children’s participation. We explain to the military parent that, even with the military parent’s formal consent, adolescents must also assent to participate in the research. We contact adolescents independently to obtain their assent only after at least one parent has formally consented to have the adolescents participate in the study.

Once we have affirmed that the family is eligible and the military parent supports their family’s participation, we send a bundle of study packets to the home, one for each person. Each packet contains a printed copy of the appropriate consent or assent documents. Parents’ packets contain three forms: a) consent for their personal participation b) consent for adolescents’ participation; and c) a copy of the assent form that we provide to their adolescents.

Finally, these packets include materials for data collection: paper copies of response cards, instructions for using electronic response cards, instructions to complete the electronic survey and a pre-incentive valued at approximately $5.

